## Introduction

Endometriosis, characterized by the presence of endometrial-like tissue outside the uterine cavity associated with chronic inflammation, affects approximately 5–10% of women of reproductive age [1–3]. This disease was first described in 1690 and primary symptoms outlined in 1769, but remains a complex and poorly understood disease [4,5]. Endometriosis symptoms are highly heterogeneous, with the most common triad being dysmenorrhea, dyspareunia and chronic pelvic pain. These symptoms can severely impair quality of life (QoL) and contribute to infertility, as previously documented [6–10].

To assess the impact of endometriosis on QoL, several validated scales have been developed. Among these, the generic multidimensional SF-36 questionnaire and the disease-specific EHP-30 scale are the most widely used tools in endometriosis research [11]. Diagnosis and management of endometriosis however, remain challenging, with an average period of 7–8 years between the onset of symptoms and diagnosis, depending on disease severity [12].

Treatment strategies are tailored, based on symptoms, patient age, pregnancy wish, lesion type and comorbidities. Despite frequent use of hormonal therapies as first-line treatment, for refractory patients and certain lesion types, surgery remains the gold standard [13].

A common postoperative complication of gynecological surgery including endometriosis surgery, is peritoneal adhesion formation, which can result in chronic pain, dyspareunia, infertility and gastrointestinal disorders, with significant short- and long-term morbidity [14–16]. Studies report that more than 90% of abdominal surgeries result in adhesions [17–19]. While minimally invasive techniques such as laparoscopy may reduce adhesion formation risk, they cannot entirely prevent adhesion development or recurrence [14,20–24]. Furthermore, endometriosis itself is considered highly adhesiogenic [14,16,25].

During abdominal surgery, a series of events occur at a tissue trauma site, resulting in the formation of adhesions. This process begins with an inflammatory reaction, followed by increased microvascular permeability, the formation of inflammatory exudate, fibrin deposition, invasion by fibroblasts, and ultimately, the development of fibrous tissue connecting the traumatized surfaces [26,27].

To address adhesion formation, various strategies and devices have been introduced, primarily involving physical barriers such as synthetic anti-adhesive membranes, fluid agents, and pharmacological treatments. These barriers act as temporary protective layers over operated surfaces during healing [28,29]. However, their efficacy is largely controversial, with inconsistent outcomes reported in the literature [16,17,21,22,30,31].

Adhesiolysis remains the only treatment for adhesions, but as recurrence following surgical adhesiolysis is common [14,22,23,26], preventing adhesions [15,22,32] relies on quality surgical techniques. Given the high level of morbidity associated with pelvic adhesions, there is a growing need for innovative, non-invasive strategies, such as manual osteopathic visceral mobilizations.

Case reports have suggested that soft-tissue mobilization techniques may provide relief from pain associated with post-surgical adhesions [33–35]. Wassermann’s review reported that immediate application of scar release techniques such as massage, visceral mobilization and myofascial release postoperatively, may prevent ileus, reduce analgesic use and potentially decrease adhesion formation [36]. Wurn et al. also highlighted the role visceral manipulation may play in improving fertility in patients with abdominopelvic adhesions [37].

The primary goals of these mobilization techniques are twofold; firstly to reduce the likelihood of adhesion development through early, repeated and adequate mobilization of postoperative areas, so as to disrupt the formation of adherent tissue, and secondly, to facilitate lymphatic drainage of the abdomen, enabling rapid absorption of intraperitoneal fluids and their reintegration into the circulatory system [38].

While traditional methods such as physical barriers and adhesiolysis, provide limited success, manual osteopathic visceral mobilizations offer a promising alternative. Further research is required to confirm their effectiveness, hone methodologies, and establish evidence-based protocols to alleviate the burden of adhesion-related complications.

We present the protocol for a superiority, prospective, monocentric, randomized, phase II controlled trial with a 2:1 parallel group design. The primary objective of this trial is to evaluate the impact of osteopathic visceral mobilizations on postoperative quality of life in women undergoing surgery for endometriosis. Intervention includes postoperative consultations with an experienced osteopath and training in abdominal self-mobilization, with outcomes assessed at 12 months post-surgery. Secondary objectives include comparing patient quality of life at 6 and 12 months post-surgery, post-operative pelvic pain, scar appearance, abdominal flexibility, range of medical and non-medical care, use of analgesics and hormonal treatments, pregnancy achievement documented at 12 months, physical activity and sedentary lifestyle and patient compliance throughout the study.

This protocol provides a robust framework for investigating the effectiveness of osteopathic interventions in improving postoperative outcomes and quality of life in this patient population.

## Materials and methods

### Setting

The study will be conducted in an academic tertiary referral hospital in Clermont-Ferrand, France which is one of the 5 national expert centers for the management of endometriosis.

This research has obtained the written ethical approval of the French Personal Protection Committee Sud-Est III on July 31, 2024 (2023-A02653-42).

### Study design and participant timeline

The flow chart of the study is presented in **Fig 1**. This is a superiority monocentric 2:1 randomized parallel group trial comparing reported quality of life, using the 30-item Endometriosis Health Profile (EHP-30) questionnaire, in 2 groups of patients operated for endometriosis. In the experimental group, patients receive pre and post-operative osteopathic consultations. The pre-operative consultation includes learning abdominal self-mobilizations and abdominal diaphragmatic respiration with the osteopath. The 5 post-operative consultations, occurring at 3–5 day intervals, involve visceral mobilizations performed by the osteopath (D6, D10, D14, D18 and W6). In the second group (control group), patients receive no osteopathic mobilizations (**Fig 2**).

**Fig 1 pone.0323214.g001:**
[figure not shown]
Flowchart of MOVENDOP trial.

**Fig 2 pone.0323214.g002:**
[figure not shown]
Flow diagram of MOVENDOP trial.

Both groups benefit from 3 post-operative consultations with the surgeon (at 6 weeks, 6 and 12 months after surgery) and an osteopathic consultation 1 year after surgery for endpoint assessment (abdominal flexibility). In addition, the control group receives training in visceral self-mobilization. Data from patients, surgeons and osteopaths is collected at baseline (pre-operative visit), surgery, post-operative consultations (6 weeks, 6 and 12 months after surgery), 5 post-operative osteopathic interventions and at 1 year after surgery (**Fig 1** and **Fig 2**).

A follow-up booklet distributed to patients according to their randomization group, will allow patients in the experimental group to provide data concerning abdominal self-mobilizations performed during the first year following surgery (frequency of performing osteopathic maneuvers and evaluation of pain), and for both groups to provide data on abdominal flexibility at 12 months, medical and non-medical treatment received, and analgesic and painkiller use during this period.

### Population

Inclusion criteria are patients aged > 18 requiring surgery for infiltrating endometriosis, who are able to give informed consent for participation in MOVENDOP research and the NoEndo cohort, the French National Observatory for ENDOmetriosis developed by Clermont-Ferrand University Hospital (ethical approval 2022-CF037), data being mostly collected via the NoEndo digital platform.

Non-inclusion criteria include patients with an indication for surgery for superficial endometriosis, patients under guardianship, trusteeship or legal protection, pregnant or breastfeeding patients, patients non- affiliated to the French social security system, non-French speakers, refusal to participate or patients participating in another study.

### Recruitment and consent

Patients will be recruited during the pre-operative consultation by one of the surgeons involved in this study, and receive information on research objectives and procedures. All patients will benefit from a minimum seven-day reflection period. The second consultation with the surgeon is dedicated to providing further information and the signing of consent forms. Based on the number of surgeries for infiltrating endometriosis performed in our service, the rate of inclusion is estimated at 3 patients per month. The period of participation by patient is one-year post-surgery.

### Blinding

For both groups, osteopathic consultation at 1-year post-surgery is carried out by an independent osteopath, blind to patient group allocation. Abdominal tissue flexibility will be evaluated for all participants at this consultation.

### Intervention

#### Surgical technique.

Our surgical technique has previously been described [8,39]. Endometriosis staging is performed after surgery based on rAFS scores. Using laparoscopy as an exclusive approach, complete surgical treatment of endometriosis will be performed, which allows accurate disease stage classification. Superficial peritoneal lesions will be treated using bipolar coagulation or peritoneal excision, and endometriomas by cystectomy as described previously [40]. Recto-vaginal nodules will be treated by shaving or by colorectal resection should a shaving procedure be deemed unsatisfactory. This surgical technique has been previously detailed [41]. In cases of endometriosis invading the sigmoid colon or the small bowel, segmental resection will be performed and ureteral involvement treated by ureteroneocystostomy where necessary, as previously described [42]. In the event of bladder lesions invading the mucosa, a partial cystectomy will be performed and closed using single- or double-layer suturing.

Post-operative consultations with the surgeon (at 6 weeks, 6 and & 12 months) will allow assessment of pain, scarring and post-operative complications.

#### Osteopathic interventions.

Patients in the experimental group will receive training in abdominal self-mobilizations at an initial pre-operative consultation, to ensure they can perform these techniques independently and take an active role in their treatment. While some maneuvers remain managed by the osteopath, patients are required to perform frequent sessions of self-mobilization of the abdomen, combined with Abdominal Diaphragmatic (AD) breathing. AD breathing, the self-mobilization procedure and osteopathic intervention are detailed in appendix 1 and 2.

Patient participation allows:

Optimization of treatment provided by the osteopath, who cannot be seen every dayPain management using the simple tools available to patientsAssociation of this part of the body with sensations other than painPatients to take an active role in their treatment.

Patients in the intervention group receive six sessions with the osteopath.

**Session 1** Pre-surgical session focusing on the teaching of self-mobilization **(****Appendix 1**)

AD breathing in 6 stepsAbdominal self-mobilization of:Three lower abdominal regions: right iliac fossa, hypogastrium and left iliac fossaAbdominal scarsSequence of maneuvers and repetitions:Ten AD breathsAbdominal self-mobilizations (of the 3 regions + scars)10 AD breaths

The procedure is to be repeated 3 times a day during the first month.

In the first postoperative week if self-mobilizations are difficult to perform (e.g., high pain levels or apprehension), the patient will perform AD breathing more frequently, namely 6 cycles of 10 AD breaths per day.

**Sessions 2–6** (D6, D10, D14, D18 and W6): Visceral mobilizations by the osteopath are performed during the month following surgery, with sessions at 3–5-day intervals (Appendix 2, **Fig 1** and **Fig 2**).

During these consultations, the osteopath ensures self-mobilizations are being correctly carried out, readjusts if necessary and answers any patients questions. The osteopath also checks that patient follow-up notebooks are completed.

These sessions also involve:

a/Achieving a balanced diaphragmatic rangeb/General abdominal mobilizations: hypogastric zones and right and left iliac fossaec/Abdominal scar manipulationd/Maneuver stages:Ten AD breathsWork on achieving balance in diaphragmatic rangeGeneral abdominal mobilizationsTen AD breaths

After the first postoperative month, the patient performs the self-mobilizations on a daily basis during the week following menstruation. In patients whose cycle is blocked by contraception, the procedures are recommended as analgesic in the event of abdominal pain.

Explanations and demonstrations given by the osteopath ensure correct understanding and sequence performance by the patient.

Patients receive a summary document and access to an online video and are requested to note the frequency and periodicity of the sequences performed, on an online document.

**Session at one-year** All patients in both groups will be seen one year after surgery for an osteopathic consultation with a dual aim:

a/Evaluation of abdominal flexibility

Assessment of abdominal flexibility is performed by the osteopath using the mobilizations of the hypogastric regions, right iliac fossa and left iliac fossa as performed during previous consultations.

Abdominal flexibility is scored by the osteopath using a visual analogue scale (VAS) ranging from 0 = maximal mobility to 10 = absence of mobility, based on the osteopath’s experience of movement in these areas. Differences in perceived amplitudes are scored for each axis of movement (up/down, in/out and clockwise/counterclockwise rotation).

In cases of pain, a second VAS is used for assessment, indicating the area and direction of the mobilization that triggered the pain, or by noting the pain score as null.

b/Self-mobilization training for control group patients:

Patients are taught self-mobilizations and the 6 cycles of AD breathing by an osteopath. They also learn how these exercises contribute to management of abdominal pain and prevention of adhesions associated with endometriosis relapse.

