### Outcomes

The primary outcome is the percentage variation in baseline EHP30 questionnaire scores between the pre-operative visit and at 1 year after surgery.

To measure QoL, the authors chose the EHP-30 questionnaire, one of the most frequently used scales for quantification of perceived health, specific to endometriosis [11].

The EHP-30 contains 30 items ranging from 0 (best health status) to 100 (worst health status). The core questionnaire items are grouped into 5 main scales: pain (11 items), control and powerlessness (6 items), emotional well-being (6 items), social support (4 items) and self-image (3 items). A modular questionnaire, that may not apply to all women with endometriosis, comprises 23 items grouped into six scales: ‘Work’ (5 items), ‘Relationship with children’ (2 items), ‘Sexual intercourse’ (5 items), ‘Medical profession’ (4 items), ‘Treatment’ (3 items), and ‘Infertility’ (4 items) [7].

Secondary outcomes are listed below:

1/- a/The following validated questionnaire scores: EHP-30, GIQLI (digestive function), FSFI (sexual function), ICIQ-FLUTS (urinary tract symptoms) and PCS (pain catastrophizing) evaluated at the pre-operative visit, and at 6 and 12 months.- b/VAS of pelvic pain reported at the pre-operative visit, then post-operatively at H6, D1, 1 month, 6 and 12 months and expressed as a percentage variation compared with pre-operative visit results.-c/Post-operative examination of scar appearance by the surgeon at 6 and 12 months using the SCAR (Scar Cosmesis Assessment and Rating) scale.2/- a/VAS of abdominal flexibility in the following areas: hypogastrium, and right and left iliac fossa, at one year assessed by an independent osteopath, scores ranging from 0 to 10 (0 corresponding to normal flexibility and 10 to total rigidity).- b/Consultations in addition to conventional care (medical and non-medical)- c)Use of analgesics and hormonal treatments reported by patients during the first postoperative year-d)Pregnancy achievement during the first postoperative year3/The International Physical Activity Questionnaire (IPAQ) assessed before surgery, at 6 and 12 months after surgery.4/Short-term compliance in terms of number of days and frequency of mobilizations, assessed on a weekly basis for up to 6 weeks,. Long-term compliance is assessed monthly post-cycle in terms of whether and how often mobilizations were performed, and if used in cases of pain.

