Comparisons at 1 year will be made using standard statistical tests visit (secondary objective 2). To investigate the dependence between two qualitative variables (including randomization group and fertility), the Chi2 test or Fisher’s exact test (depending on subject numbers) will be applied to a qualitative variable. To compare a quantitative variable (including abdominal flexibility) with a two-modality qualitative variable (including randomization group), a t-test or a Wilcoxon test will be applied, depending on distribution (Gaussian or not).

To identify patient profiles based on the sub-domains of quality of life assessed during the pre-operative visit (secondary objective 3), a factorial analysis will be carried out, followed by a classification method. A Principal Component Analysis (PCA) will be used for further detailed analysis of quantitative data. A hierarchical ascending classification (HAC), based on the results of the factorial analysis will then be carried out. To compare these different groups in terms of improvement in post-operative quality of life, analysis will be based on a comparison using a Student’s t test or a Wilcoxon test according to distribution (Gaussian or not) if classification results in a typology of 2 groups, or using an ANOVA or a Kruskal-Wallis (according to distribution) if classification results in a typology of more than 2 groups.

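### The only booklet-completeness check described takes place at sessions that only the experimental arm attends, so early analgesic recording may be fuller in that arm

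*Protocol article*

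**What the plan says.** Under Study design and participant timeline, the booklet is introduced as follows: "A follow-up booklet distributed to patients according to their randomization group, will allow patients in the experimental group to provide data" on their self-mobilizations. The same sentence has both groups use it to report "medical and non-medical treatment received, and analgesic and painkiller use during this period", the period being the first year after surgery. Under Outcomes, item 2c is "Use of analgesics and hormonal treatments reported by patients during the first postoperative year", and item 2b is consultations beyond conventional care.

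The Osteopathic interventions section describes sessions 2 to 6, at D6, D10, D14, D18 and W6. There the osteopath reviews the patient's self-mobilization technique, and: "The osteopath also checks that patient follow-up notebooks are completed". Controls have no such sessions: "In the second group (control group), patients receive no osteopathic mobilizations". Both arms see the surgeon at 6 weeks, 6 months and 12 months, and an osteopath at one year. The text describes no booklet check at any of these shared contacts.

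Data collection methods adds a second route. The surgeon and clinical research associates complete a REDCap eCRF at each visit, and its listed items include hormonal treatment and, for both groups, the extent of medical and non-medical treatment. Analgesics are not on that list. Statistical methods compares the secondary objective 2 outcomes between arms at one year with standard tests.

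**The concern.** A between-arm comparison of a self-recorded outcome needs recording to be equally complete in both arms. Here the one stated support for recording comes with the intervention itself: experimental patients are checked five times in the first six weeks, while controls have no stated check.

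A second feature works the same way. The booklet differs by arm, and the experimental version also holds the self-mobilization record, for a routine prescribed three times a day in the first month. Those patients have a daily reason to open it that controls lack.

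If blank control entries are read as no use, control analgesic use is understated. A true reduction in the experimental arm could then be masked, or appear as an increase. If blanks are treated as missing, the control figures come from the patients who recorded most diligently, and the direction of the error cannot be predicted. What is at stake is the interpretation of one secondary outcome, not the primary result.

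**Working it through.** **The plan's own figures.** There are none to reproduce on this point. The document gives no expected analgesic use and no booklet completion rate.

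**Stated completeness checks, by arm**

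| Contact | Experimental | Control |
|---|---|---|
| Osteopath at D6, D10, D14, D18, W6 | 5 checks | sessions not held |
| Surgeon at 6 weeks, 6 and 12 months | no check stated | no check stated |
| Osteopath at 1 year | no check stated | no check stated |

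The count is 5 against 0. All five fall in the first 6 of 52 weeks: 6/52 = 11.5% of the recording period.

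**Source of each outcome**

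- Analgesic use: the booklet is the only source named.
- Hormonal treatment: the visit-based eCRF, for both arms.
- Care use: the booklet and the eCRF. The eCRF list closely mirrors the booklet list, so the booklet may feed the eCRF. The text does not say.
- EHP-30: completed by patients on the NoEndo platform in both arms.

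**Size, under stated assumptions.** Assume that 95% of use is recorded when checked and 70% when not, that blanks are read as no use, and that true use is the same in both arms. Let f be the share of the year's use that falls in the checked weeks.

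Recorded share, experimental = 0.95f + 0.70(1 − f). Recorded share, control = 0.70.

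Ratio = 1 + f × (0.95 − 0.70)/0.70 = 1 + 0.357f.

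- Use spread evenly over the year, no carry-over of habit: f = 6/52 = 0.115. Experimental share = 0.95 × 0.115 + 0.70 × 0.885 = 0.729. Ratio = 0.729/0.70 = 1.04, a false excess of about 4%.
- All use in the checked weeks: f = 1. Ratio = 0.95/0.70 = 1.36, a false excess of about 36%. Full carry-over of recording habit to the rest of the year gives the same figure.

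**Effect on a true reduction.** Take a true 25% reduction, 7.5 against 10 analgesic days.

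- At f = 1: 7.5 × 0.95 = 7.1 recorded against 10 × 0.70 = 7.0. The reduction disappears.
- At f = 0.115: 7.5 × 0.729 = 5.5 against 7.0, a ratio of 0.78 where the truth is 0.75. The reduction is nearly preserved.

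**If the outcome is any use, yes or no.** Recorded proportion = true proportion × recording rate, with the recording gap applied to all use. For true use of 30% to 70% in both arms, 95% recording in the experimental arm and 90% to 70% in controls:

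- Smallest: 0.30 × 0.95 = 28.5% against 0.30 × 0.90 = 27.0%, a difference of 1.5 points (odds ratio 1.08).
- Largest: 0.70 × 0.95 = 66.5% against 0.70 × 0.70 = 49.0%, a difference of 17.5 points (odds ratio 2.07).

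**The case against.** The strongest reply has four parts.

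First, the check may not concern analgesics. Its sentence follows directly on the check of self-mobilization technique, and compliance is an outcome assessed weekly up to 6 weeks. The osteopath may be looking mainly at the self-mobilization pages. This is plausible, but the sentence as written covers the booklet without limit, and the fix would simply make the narrower reading explicit.

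Second, the article condenses a fuller protocol, which may contain a control-arm check. That is possible, and stating it would settle the point. The concern does not rest on silence alone, however: the article places the one check it describes at intervention-only sessions.

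Third, the plan has general safeguards. The Data quality section asks for an explanation of missing data and for monitoring to limit it, and Statistical methods says missing data will be quantified. These count against assuming that blanks will be read as no use. They do not equalize recording, and the mandatory fields described belong to the NoEndo platform, not to the booklet.

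Fourth, the outcome is secondary, and some secondary analyses are described as mainly exploratory. This stands and limits the weight of the point.

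A reader might also infer more than the text supports:

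- That all of outcomes 2b and 2c rest on the booklet. They do not, because the eCRF covers hormonal treatment and the extent of care at visits in both arms.
- That a 36% false excess is to be expected. It is the upper end of an assumed range and needs all use to fall in the checked weeks or full carry-over of habit.
- That controls provide no data before 6 weeks. Pelvic pain scores are scheduled at H6, D1 and 1 month without restriction by arm.
- That the trial can say nothing about analgesic use. The accurate statement is that it could not separate effect from recording.

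**Conclusion.** The point holds for analgesic use. Under the plan as written, support for completing the booklet depends on allocation in the first six weeks, and the booklet is the only named source for this outcome. A difference, or an absence of difference, between arms could reflect recording. That use concentrates in the weeks after surgery is plausible but is not stated, so the document does not locate the trial within the 4% to 36% range. That range rests on the assumed 95% and 70% recording rates and on blanks being read as no use. If blanks are so read, the error runs against the intervention. Care use is exposed only so far as the booklet feeds the eCRF, hormonal treatment less so, and the EHP-30 comparison and its sample size not at all. The change is worth making because it is cheap, but it does not bear on the trial's main conclusion.

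**What to change.** - For the between-arm comparison of analgesic use, ask the same fixed questions in both arms (class of analgesic and days of use since the last visit) at the existing 6-week, 6-month and 12-month visits. Enter the answers in the eCRF beside the hormonal treatment and care items, or collect them on NoEndo.
- Limit the osteopath's check at sessions 2 to 6 to the self-mobilization pages.
- Treat booklet analgesic entries as descriptive, and report booklet completeness by arm. The completeness report can also cover patients already enrolled, since recruitment opened in January 2025.
- State whether the care-use items in the eCRF are taken from the booklet or asked at the visit.

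The cost is a short block of questions at visits that already take place and one line in the osteopath's instructions. The downside is longer recall than with a diary, but it is equal in both arms.
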